## **8. STATISTICAL ANALYSIS**

Data will be collected in Castor EDC and exported for Statistical analysis in IBM SPSS Data will be collected in Castor EDC and exported for Statistical analysis in IBM SPSS Statistics 29.0 (SPSS Inc., Chicago, IL, USA). Data will be presented according to the Consolidated Standards of Reporting Trials (CONSORT) Statement, an international guideline on adequate reporting of RCTs. To assess whether continuous variables are normally distributed, histograms and the Kolmogorov-Smirnoff test will be computed. Continuous data will be expressed as mean  $\pm$  standard deviation (SD) when normally distributed, and as median  $\pm$  interquartile range (IQR) when skewed. Number of cases and percentages will be presented for categorical variables. A p-value of less than 0.05 will be regarded as statistically significant for all calculations.

### **8.1 Primary study parameter(s)**

The data of our primary outcome are quantitative and will be presented as frequencies and proportions. To compare the difference in recidivism (recurrent and residual disease) at 12, 36 and 60 months between both surgical groups the Chi-squared test or Fisher's exact test will be used. The relative risk (RR) and absolute risk difference (RD) will be calculated as effect sizes using a generalized linear model for binomial outcome with a log-link (for RR) and identity link (RD). The primary analysis will be adjusted for site by including centre as covariate in a logistic regression model with treatment arm as the main predictor. All effect sizes will be accompanied by 95% confidence intervals. To graphically demonstrate the rates of recidivism, recurrent and residual disease over the follow-up time, a Kaplan-Meier analysis will also be performed and survival curves will be constructed. Multiple imputation will be used to deal with missing

outcomes. A 20% difference is defined as the threshold for clinical relevance and will be consistently applied in both clinical effectiveness analyses and the health economic evaluation.

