## 3. STUDY DESIGN

The proposed study design is a multicenter two-armed randomized controlled trial. It will be conducted using a single blind method. The patients will not know which surgical approach they received, which is necessary for the subjective measurement of the quality of life questionnaire. The surgeon will know which procedure he/she has performed as this is unavoidable. The surgeon will not write down which procedure the patient received in the surgical report or in the letter to the general practitioner. It will only be recorded in Castor and in the RFS map. De blinding (single-sided) will only be lifted if it is in the interest of the safety of the participant. De participant and/or general practitioner can request this from the treating physician (ENT-surgeon) who performed the surgery. The ENT-surgeon will decide if lifting of the blinding is necessary and inform the researcher about this event. In case of emergency and in absence of the treating physician, other medical specialists can lift the blinding by checking the placement of the patient in the RFS map. All medical specialists have access to the RFS map with information of the participants where an inclusion table with randomization is stored. This way it is possible to lift blinding 24 hours a day. After completion of the last quality of life questionnaire (at 36 months) the treatment group will also be added to the patient file in HiX. The patients are randomly assigned to one of the two groups (A or B). A web-based randomization tool in Castor will be used for the allocation and will be accessed by the researcher. The study will be conducted with a sufficient duration to gather the sample size needed. The setting is multi-center; both secondary and tertiary university hospitals will participate. The estimated duration of the study is 7 years (84 months): 1 year will be allocated for completing the inclusions and follow-up will be completed in the following 5 years. The last year will be used to analyze the data and round up the trial.

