All pre-operative measurements are part of standard care in the Netherlands and Belgium. Pre-operatively patients receive an audiometric exam, a physical examination of the ear, a CT-scan and fill in the patient-reported outcome measure (PROM). Follow-up will be planned at least at 6-18 weeks, at around 1 year and at around 3 years after surgery. It is important to note that conducting a CT scan and audiometry preoperatively as well as the DW-MRI's after 1 and 3 years are part of the standard care. In line with standard care, if there is a suspicion for recurrent or residual pathology (either clinically by micro-otoscopy or radiologically by DW-MRI) the treating physician will perform a revision surgery. If during revision surgery the suspicion is confirmed, the type of recidivism (residual or recurrent) is recorded and the follow-up of the patient ends. Data that is collected up until the point of detection of residual or recurrent disease will be used for analysis (this is not an exclusion criterium). If the suspicion is not confirmed (false-positive) then the patient will continue the follow-up as planned (unless a reconstructive procedure with the goal of improving hearing has been performed). During the three years of follow-up, patients should not undergo another type of ear surgery. If this is unavoidable, as judged by the treating physicians, the patient will be retrospectively excluded. In order to ensure that the same surgical data is collected in all participating centers, a standardized operation report will be written and shared by the sponsor (UMC Utrecht). This operation report will be recorded in the electronic patient dossier (with the exception of the information if obliteration was used or not) and transferred to Castor EDC. In Castor there will be a variable to also record if obliteration has taken place or not. The only methodology that is different to standard care is the randomization of the patients and the completion of the questionnaire. It is important to note that the technique used for the obliteration technique differs slightly between centers. The exact surgical technique will be described by the participating otologists and included in the description of the study, for example in a publication.

**Figure 1.** Flowchart of the study. *Standard care is indicated by \**[figure not shown]

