#### 4.4 Sample size calculation

To detect a clinically relevant outcome of the primary objective (residual or recurrent disease) a sample size of at least 160 participants is needed. To calculate the sample size we used applicable and recent retrospective results of the UMC Utrecht (from January 2015 to March 2020) and reported recurrence rates from a systematic review of the literature, as this represents the most methodologically comparable and robust dataset currently available. We used our results to calculate the sample size needed with a power of 0.80. Relevant clinical difference was set at 20%. The calculation is based on a two independent proportions power analysis using a Z test with pooled variance with a alpha of 0.05 and a power of 0.80. Sample size calculations were performed with PASS 2008 and resulted in 80 patients per arm. To compensate for potential dropouts, a 10% margin is implemented, **resulting in 178 patients in total.**

| Two Independent Proportions (Null Case) Power Analysis                    |                               |                               |                                     |                                   |                     |                     |                 |                 |        |
|---------------------------------------------------------------------------|-------------------------------|-------------------------------|-------------------------------------|-----------------------------------|---------------------|---------------------|-----------------|-----------------|--------|
| Numeric Results of Tests Based on the Difference: P1 - P2                 |                               |                               |                                     |                                   |                     |                     |                 |                 |        |
| H0: P1-P2=0. H1: P1-P2=D1<>0. Test Statistic: Z test with pooled variance |                               |                               |                                     |                                   |                     |                     |                 |                 |        |
|                                                                           | Sample
Size
Grp 1
N1 | Sample
Size
Grp 2
N2 | Prop H1
Grp 1 or
Trtmnt
P1 | Prop
Grp 2 or
Control
P2 | Diff
if H0
D0 | Diff
if H1
D1 | Target
Alpha | Actual
Alpha | Beta   |

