## 6. METHODS

### 6.1 Study parameters/endpoints

#### 6.1.1 Main study parameter/endpoint

The main endpoint is the number of patients with recurrent or residual cholesteatoma. Follow-up for recurrent/residual cholesteatoma will be performed after 6-18 weeks and after approximately 1, 3 and 5 years. Follow-up is done by micro-otoscopy and DW-MRI scans (after 1, 3 and 5 years) (see figure 1 for the follow-up steps). A newly formed retraction pocket from the tympanic membrane correlates with recurrent disease (clinical diagnosis), whereas cholesteatoma formation behind a normal or an intact tympanic membrane after primary surgery correlates with residual disease (radiologic diagnosis).

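### Recidivism is tested at 12, 36 and 60 months, each at p<0.05, with no primary time point named; if any one result may count as success, the false-positive chance is roughly 9-12%, not 5%

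*Protocol*

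**What the plan says.** - Section 6.1.1 defines the endpoint without a time: "The main endpoint is the number of patients with recurrent or residual cholesteatoma". Assessment runs to about five years.
- Section 8.1 tests it three times: "To compare the difference in recidivism (recurrent and residual disease) at 12, 36 and 60 months between both surgical groups". The method named for these comparisons is that "the Chi-squared test or Fisher's exact test will be used". The section then adds "The primary analysis will be adjusted for site by including centre as covariate in a logistic regression model", again with no time stated. Kaplan-Meier curves are for display.
- Section 8 sets the threshold: "A p-value of less than 0.05 will be regarded as statistically significant for all calculations".
- Section 4.4 sizes the trial for one two-sided comparison: "To detect a clinically relevant outcome of the primary objective (residual or recurrent disease) a sample size of at least 160 participants is needed". Its table gives 80 per arm, 20% against 40%, power 0.8009 and actual alpha 0.0472. Adding 10% for dropout gives 178. Neither text nor table says when after surgery the two rates apply.
- Section 8.2 does fix the time of inference for lesser outcomes: 12 months for hearing and 36 months for the OQUA.
- Section 3 is not consistent about the horizon. It allots five years to follow-up, yet also says "During the three years of follow-up, patients should not undergo another type of ear surgery". Section 6.1.1, Table 1 and Section 8.1 all take the primary outcome to 60 months.

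**The concern.** Three tests of the primary outcome, each at 0.05, with no order, combination rule or adjustment, leave open what counts as a positive trial. A difference at 12 months only, or at 60 months only, could be reported as the primary result. The 5% error rate used in Section 4.4 belongs to one test and does not carry over to a best-of-three reading.

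Power has the same gap. A sample size for 40% against 20% is tied to the time at which those rates occur. Cumulative recidivism is lower earlier, so the same 80 per arm gives less power at an earlier time if the rates describe a later one.

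This is more than detail a protocol may leave to a statistical analysis plan. The protocol itself fixes the three comparisons and the threshold, and its sample size depends on the choice of time.

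**Working it through.** **Inputs from the protocol.** 80 per arm, rates 0.20 and 0.40, two-sided alpha 0.05, pooled-variance Z test and 10% dropout (Section 4.4); three test times (Section 8.1); 0.05 for each test (Section 8).

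**Inputs assumed.** The cumulative rates at 12 and 36 months, which the protocol does not give. Several patterns are used.

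**1. The protocol's own figures.** The statistic is z = (p1 − p2) / √[2·p̄(1 − p̄)/n], with p̄ the mean of the two observed proportions and n = 80. Enumerating all pairs of binomial counts and rejecting when |z| > 1.96 gives power 0.8009 for 0.20 against 0.40, and alpha 0.0472 with both arms at 0.40. Both match the table. 160/0.90 = 177.8, so 178. The stated design is therefore correct for one test.

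**2. False-positive chance with three tests.** If the tests were independent, it would be 1 − 0.95³ = 14.3%. They are not: a patient with an event by 12 months is still a case at 36 and 60 months. Under equal rates, the correlation between the statistics at times i < j is √[p_i(1 − p_j) / (p_j(1 − p_i))]. For 10% and then 30%, that is √(0.10 × 0.70 / (0.30 × 0.90)) = 0.51.

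Simulating cumulative counts with equal rates in both arms (80 per arm, 400,000 trials per pattern, the pooled test at each time) gives the chance of at least one p<0.05:

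| Assumed cumulative rates at 12/36/60 months | Chi-squared | Fisher's exact |
|---|---|---|
| 10/20/30% | 11.2% | 7.2% |
| 13/27/40% | 11.3% | 7.5% |
| 10/25/40% | 11.7% | 7.7% |
| 5/20/40% | 11.8% | 7.1% |
| 20/30/40% | 10.4% | 7.1% |
| 30/36/40% | 8.8% | 6.0% |

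The value is lowest when most events come early, because the three tests then nearly repeat one another.

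**3. Power by time point.** Suppose 40% against 20% is reached at month 60 and a risk ratio of 0.5 holds throughout. The assumed control rates are 15/30/40% and the obliteration rates 7.5/15/20%. The enumeration of step 1 gives:

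| Month | Rates | Difference | Power, one test at 0.05 |
|---|---|---|---|
| 12 | 15% v 7.5% | 7.5 points | 0.32 |
| 36 | 30% v 15% | 15 points | 0.63 |
| 60 | 40% v 20% | 20 points | 0.80 |

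**4. Two ways to restore 5%.** With one primary time, the error rate is 5% nominal (4.7% in the protocol's table) and 80 per arm keeps power 0.80, provided 40% and 20% are the rates at that time. With three tests at 0.05/3 each, the normal approximation puts power at 80 per arm at about 0.65 for 40% against 20%. Restoring 0.80 needs 109 per arm: 218 in total, and 218/0.90 = 242.2, so 243 with dropout.

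**The case against.** Several points can fairly be made for the protocol.

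- **No rule that any one result wins is written down.** Section 8.1 also speaks of its primary analysis in the singular, and that analysis is a centre-adjusted logistic model, which was not simulated. This stands as a limit: the inflation is conditional. But that model has no time attached either, so it does not settle which result decides the trial.
- **The size rests on assumed rates and on the test chosen.** This stands, and is why a range is given. Fisher's exact test would bring it to about 6-8%. At most of the rates considered, expected counts are 5 or more (80 × 0.10 = 8), so chi-squared would normally apply. At 5% by month 12 the expected count is 4, and Fisher's test could be used there.
- **Multiplicity procedures often sit in the analysis plan.** True of the procedure. The time to which the sample size refers is a matter for the protocol.

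Two stronger readings are tempting, and the documents do not support them.

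- A reader might infer that the 60-month comparison counts only patients still in follow-up, because Section 3 ends follow-up at a confirmed event. But Section 6.1.1 counts patients with disease, and Section 3 keeps data up to detection in the analysis. The cumulative reading is the natural one and only needs stating.
- A reader might infer that blinding of the primary outcome is broken before month 60, because after the last questionnaire ("at 36 months) the treatment group will also be added to the patient file in HiX") the allocation is released. But Section 6.2 blinds participants only, and Section 3 ties that blinding to the questionnaires, which end at month 36. Blinding assessors to month 60 would be a separate design preference.

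**Conclusion.** The concern holds in this form: the protocol tests its primary outcome at three times at 0.05 each, names none as primary, and leaves the design rates without a time. Read so that any one significant result counts as success, the false-positive chance is roughly 9-12% with chi-squared tests, against the 5% of Section 4.4. That range rests on assumed interim rates and already allows for the correlation between the tests. It is not a fixed 11%, and the 14.3% for independent tests would overstate it.

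The 80% power is correct arithmetic for one comparison at whichever time the rates are 40% and 20%. The 0.32 and 0.63 at earlier times illustrate one assumed course. The documents do not show that the design rates belong to month 60. The three-year wording in Section 3 is a lesser inconsistency that adds to the doubt about which horizon is meant.

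This should be corrected before any outcome data are seen; after that, the choice of time could no longer be shown to be prespecified.

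**What to change.** - **Section 8.1:** name one primary time point. Month 60, where follow-up for the primary outcome ends, is the natural candidate, but the sponsor should choose. Define the outcome there as cumulative recidivism since surgery, so that an event found earlier remains an event. Test it once at two-sided 0.05 with the centre-adjusted model.
- **Other two times:** report them as supportive estimates with 95% confidence intervals and no claim of significance.
- **Section 4.4:** check the retrospective data and the review behind the 40% and 20%, and state which time after surgery they describe. If it is not the chosen time, restate the power there.
- **Section 3:** reconcile the three-year wording with the five-year follow-up in Section 6.1.1, Table 1 and Section 8.1. Because that sentence also governs other ear surgery, how it should read is for the investigators to settle.

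**Cost.** Significance claims at the two other times are given up. If the design rates belong to the chosen time, the change is wording only and the total stays at 178. If they do not, the power statement, and possibly the sample size, must be reworked.

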| OQUA      | Otology Questionnaire Amsterdam                                                                                                                                                                                        |

|                   |                                                                                                                                                                                                                                                                                                                                                  |
|-------------------|--------------------------------------------------------------------------------------------------------------------------------------------------------------------------------------------------------------------------------------------------------------------------------------------------------------------------------------------------|
| PROM       | Patient-reported outcome measure                                                                                                                                                                                                                                                                                                          |
| PSA        | Probabilistic sensitivity analysis                                                                                                                                                                                                                                                                                                        |
| Recidivism | Total number/rate of residual and recurrent disease                                                                                                                                                                                                                                                                                       |
| (S)AE      | (Serious) Adverse Event                                                                                                                                                                                                                                                                                                                   |

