The goal of cholesteatoma treatment is to eradicate the disease and create a safe and dry ear, while preventing recurrence of pathology and preserving, or even optimizing, hearing. The best surgical approach has been subject of debate for decades. The two traditional approaches are: canal wall down (CWD) and canal wall up (CWU) tympanomastoidectomy. Although they both have their advantages and disadvantages, the CWU technique has increasingly become the standard approach. CWD surgery results in a radical cavity, which gives a wide visual exposure of the disease for removal and therefore minimizes the chance of leaving cholesteatoma behind. However, a radical cavity creates a situation that requires regular debridement, increased risk of recurrent infections, and makes the fitting of hearing aids more challenging. The CWU approach on the contrary, maintains the normal anatomy of the bony part of the ear canal. It results in less frequent inflammations, hearing aids fit better and the regular outpatient cleaning of the ear is not indicated (1,2). However, the major issue with the CWU treatment is the higher odds of recurrent and residual disease. Whereas CWD tympanomastoidectomy show recidivism - including both recurrent and residual disease - rates of 0 to 17%, CWU tympanomastoidectomy rates vary between 9% and 70% (3,4).

Over the past decade, there has been growing interest in finding ways to decrease the disease recurrence rates and improve post-operative hearing outcomes. One promising technique is the obliteration of the mastoid and epitympanic area after either CWD or CWU tympanomastoidectomy. Obliteration is the act of filling the cavity that is created to reach the middle ear with either bone dust (sometimes also referred to as bone pâté) or artificial material. The purpose is to create a situation in which the obliteration material prevents the tympanic membrane from retracting and therefore lowers the chance of cholesteatoma recurrence. Mercke was one of the first otologic surgeons to present promising outcomes after obliteration in combination with CWD tympanomastoidectomy (5).

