When Mercke first presented his results, the so called 'diffusion weighted magnetic resonance imaging' (DW-MRI) was not yet developed, making the detection of cholesteatoma during follow-up more difficult. At this time, patients traditionally underwent a 'second-look' operation, meaning that after a certain period the ear was surgically opened again to check if the disease had come back. Surgeons that are opposed to or do not utilize the obliteration technique may be afraid that it might be more challenging to detect and remove a cholesteatoma that might have been left behind after obliteration. "The main limitation of the technique is the inability to explore the mastoid cavity during follow-up with the risk of developing a "silent cholesteatoma", making radiological follow-up essential"(6). The development of the DW-MRI changed this somewhat by providing more diagnostic assurance and is currently used for the follow-up of patients that have been operated on. With the invention of the DW-MRI, the obliteration technique was therefore reintroduced and performed also subsequent to the CWU approach as patients could be followed more reliably and more otologists started believing in and using the obliteration technique. However, a limitation of radiological follow-up is the sensitivity of a DW-MRI, which ranges from 40-100% and the fact that cholesteatoma's are only detected when they are larger than 3mm in size (7–16).

Recently, van der Toom et al. showed in their systematic review that mastoid obliteration seems to reduce recurrence rates for both the CWD and CWU approach when compared to CWD and CWU without obliteration (17). While they found recurrent and residual disease rates of 5.9% and 5.8%, respectively, for the CWD technique, the outcomes for CWU tympanomastoidectomy were better. For the latter technique, they presented a recurrent disease rate of 0.28% and a residual disease rate of 4.2%. Combining the CWU tympanomastoidectomy and obliteration technique therefore seems a good solution to preserve the normal anatomy of the ear canal, as well as minimize the chance of contracting recurrent or residual cholesteatoma.

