## 2. OBJECTIVES

**Primary Objective:** The primary aim of this randomized controlled trial is to determine whether CWU tympanomastoidectomy with obliteration reduces the recurrence and residual rates of cholesteatoma compared to CWU tympanomastoidectomy without obliteration.

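### The objective speaks of lowering the recurrence and residual rates, but only their total has a planned between-arm effect estimate, and the Kaplan-Meier curves for each type censor a competing event

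*Protocol*

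**What the plan says.** **Objective.** Protocol section 2 asks whether "CWU tympanomastoidectomy with obliteration reduces the recurrence and residual rates of cholesteatoma compared to CWU tympanomastoidectomy without obliteration". The Summary and the end of section 1 say much the same.

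**Endpoint.** Section 6.1.1 states: "The main endpoint is the number of patients with recurrent or residual cholesteatoma". The list of definitions gives recidivism as "Total number/rate of residual and recurrent disease".

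**Analysis.** Section 8.1 applies a chi-squared or Fisher test "To compare the difference in recidivism (recurrent and residual disease) at 12, 36 and 60 months between both surgical groups". It then names a relative risk (RR), an absolute risk difference (RD), a centre-adjusted logistic model and 95% confidence intervals, without naming any other outcome. The two types are mentioned separately only here: "To graphically demonstrate the rates of recidivism, recurrent and residual disease over the follow-up time, a Kaplan-Meier analysis will also be performed".

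**Recording of type.** Under section 3, the type is recorded when recidivism is confirmed at revision surgery, and the patient's follow-up then ends.

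**Expected behaviour of the two types.** Section 1 says that the obliteration material "prevents the tympanic membrane from retracting and therefore lowers the chance of cholesteatoma recurrence". It also reports the worry of some surgeons that it "might be more challenging to detect and remove a cholesteatoma that might have been left behind after obliteration".

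**The concern.** The objective names two rates, while the inferential analysis covers their sum. For many composites that is only loose wording. Here the protocol's own rationale gives reason to expect the components to behave differently. The mechanism it describes acts on retraction, and so on recurrence. The reservation it reports about the technique concerns disease left behind, which is residual disease. A fall in the total can then be driven by recurrence alone, with residual disease unchanged or higher.

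The planned curves do not settle this. Because follow-up stops at the first confirmed event of either type, a Kaplan-Meier curve for residual disease has to treat patients with recurrence as censored. That estimates the residual risk in a hypothetical setting without recurrence. It lies above the observed risk, and by more in the arm with more recurrence. If obliteration lowers recurrence, that arm is the control arm, so the curves tend to understate a rise in residual disease.

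At stake is what a positive result may be said to show. Type is recorded for every confirmed case, so the data for a direct comparison will exist, but section 8.1 specifies no effect size or interval for it.

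**Working it through.** **1. Reproduce the plan's figure.** Inputs from section 4.4: rates 20% and 40%, two-sided alpha 0.05, pooled Z test, 80 per arm. Exact binomial enumeration of that test gives power 0.8009 and, with both rates at 40%, actual alpha 0.0472. Both match the table. The normal-approximation formula gives 82 per arm, and power 0.794 at 80. Total with the 10% margin: 160/0.9 = 177.8, so 178. The calculation uses one pair of proportions, for the composite.

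**2. Split the composite.** The protocol does not divide 40% and 20% by type, so every split below is an assumption. All rows keep the composite at 40% v 20%. Rates are control v obliteration.

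| Recurrent | Residual | Residual RD (points) | 95% half-width (points) | Chance that the residual difference is significant |
|---|---|---|---|---|
| 28% v 4% | 12% v 16% | +4 | 10.7 | 0.11 |
| 30% v 5% | 10% v 15% | +5 | 10.2 | 0.15 |
| 30% v 2% | 10% v 18% | +8 | 10.7 | 0.30 |
| 30% v 0% | 10% v 20% | +10 | 11.0 | 0.42 |
| 35% v 10% | 5% v 10% | +5 | 8.1 | 0.21 |

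Formula: SE = sqrt[p_c(1 - p_c)/80 + p_o(1 - p_o)/80]. For the first row: sqrt(0.12 × 0.88/80 + 0.16 × 0.84/80) = sqrt(0.00132 + 0.00168) = 0.0548. Half-width 1.96 × 0.0548 = 0.107. Interval 4 ± 10.7, or -6.7 to +14.7 points. The last column is the exact rejection probability of the pooled Z test at 80 per arm.

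**3. What the Kaplan-Meier curves would show.** Assume that the two cause-specific hazards are proportional over time within each arm. With composite risk F and residual share s of all events, the Kaplan-Meier curve for residual disease ends at 1 - (1 - F)^s. First row:

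- Control: F = 0.40, s = 0.12/0.40 = 0.30, so 1 - 0.60^0.30 = 14.2%, against an observed risk of 12%.
- Obliteration: F = 0.20, s = 0.16/0.20 = 0.80, so 1 - 0.80^0.80 = 16.3%, against an observed risk of 16%.

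The contrast falls from 4 points to 16.3 - 14.2 = 2.1 points.

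**4. Event counts for a component model.** At 4% of 80, the obliteration arm in the first row has 0.04 × 80 = 3.2 expected recurrences. At the 0.28% that section 1 cites for canal wall up surgery with obliteration, it has 0.0028 × 80 = 0.2. Log-link or identity-link binomial models with centre terms are liable to fail at such counts.

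**The case against.** The best defence is that the composite is declared openly and used consistently: in the endpoint, the definition, the sample size and the test. Testing a declared composite is legitimate, and the objective can be read as a loose name for it. This stands. The primary test needs no change, only the objective's wording and the supporting estimates.

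A reader might infer that the components are not estimated at all, or that a rise in residual disease would be hidden. The protocol does not support either reading. Kaplan-Meier is an estimator, and section 8.1 plans curves for both types. Type is recorded for each confirmed case, and section 8 promises numbers and percentages for categorical variables. What is missing is a stated between-arm effect size and interval, and the planned curves can distort the contrast.

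It may also be said that component estimates belong in the statistical analysis plan, which is not at hand and may contain them. That is fair for the estimates. It does not cover the objective's wording or the choice of Kaplan-Meier for each type, both of which the protocol fixes.

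Nor does the protocol predict a rise in residual disease. Section 1 attributes the worry to surgeons who oppose or do not use the technique, adds that diffusion-weighted MRI has eased it somewhat, and cites residual disease of only 4.2% after canal wall up surgery with obliteration. The splits in the table show what is possible, not what is expected.

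Finally, if residual disease is harder to detect under the obliteration, fewer cases would be confirmed in that arm, and a risk difference on confirmed cases would favour obliteration. This stands as a limit of the remedy.

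**Conclusion.** The concern holds in a limited form. Section 8.1 names a between-arm test, RR, RD and confidence interval only for total recidivism, while the objective speaks of both rates. The separate curves censor a competing event and can shrink a between-arm difference in residual disease. A significant composite would not establish that both rates fell.

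Under the assumed splits, a composite success at 80 per arm is compatible with residual disease rising by 4 to 10 points. Such a rise would reach significance with probability 0.11 to 0.42, with interval half-widths of about 8 to 11 points. The fall from 4 points to about 2 on the curves also assumes proportional cause-specific hazards. The logical point depends on none of these figures.

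**What to change.** In the protocol:

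- Keep the composite as the single primary test.
- Reword the primary objective to: reduces recidivism (recurrent or residual cholesteatoma). Align the Summary and the end of section 1.
- In section 8.1 add, at the 12, 36 and 60 months already listed, the count by arm and the RD with 95% CI (RR where events allow) for recurrent and for residual disease, classified by first confirmed type. Label these as descriptive. Use an interval method suited to few events, not the centre-adjusted generalized linear model.
- Replace the Kaplan-Meier curves for each type with cumulative incidence curves that treat the other type as a competing event. The Kaplan-Meier curve for total recidivism can stay.
- State that any claim about one type rests on its own estimate.

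The cost is wording and a few extra estimates from data already collected, with no more patients and no use of alpha. The component intervals will be wide, about ±11 points under most of the assumed splits. Residual disease that goes undetected under the obliteration would still be undercounted, and the report should say so.
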